### Patient and public involvement

We engaged the University of New South Wales to convene a community reference panel to provide input and feedback into the design of the research and study procedures. The panel involved 10 members from the study target audience who were involved in two separate consultations in 2021.

### Study setting

The trial will be conducted at primary healthcare services in metropolitan and rural settings in Australia with:

High caseloads of people who currently or previously injected drugs and are at risk of HCV infection.A general practitioner and/or a nurse practitioner experienced in testing and treating HCV.

### Recruitment

Eligible clinics will be identified through consultation with government, community, clinical and research networks in viral hepatitis in Australia. Within clinics, potentially eligible participants will be approached by a clinician, nurse or community health worker. Participant-facing study promotion including posters and leaflets will be used at the discretion of participating clinics.

### Participant eligibility

Study inclusion criteria for participants are as follows:

Current or former injecting drug use (ie, injected drugs at least once).Aged 18 years or over.Attending a participating primary healthcare for any reason.No previous treatment with DAAs.Medicare eligible.Able to speak and understand English.

Exclusion criteria are as follows:

Women known to be currently pregnant or who are breast feeding.Individuals currently engaged in HCV treatment.Unable to provide informed consent.Tested for HCV in the past 3 months.Previous successful treatment with interferon-based therapy for HCV.

### Study arms

This study will implement three intervention arms and a control arm, as shown in figure 1. Final recruitment, retention and outcome assessments will be presented in accordance with the Consolidated Standards of Reporting Trials (CONSORT) statement, including CONSORT diagrams. Arm A will implement a rapid POC antibody test in addition to SOC confirmatory RNA testing and blood tests at the baseline visit. Arm B will implement a rapid POC antibody and POC RNA test in addition to SOC blood tests at the baseline visit. Arm C will implement a rapid POC antibody test and same-day treatment with DAAs for antibody-positive participants, in addition to standard blood tests. The control arm will implement the SOC in operation at each clinic.

**Figure 1 F1:**
[figure not shown]
(A) Sequence of events in arm A: rapid HCV antibody testing followed by standard of care. (B) Sequence of events in arm B: rapid HCV antibody±rapid HCV RNA followed by standard of care. (C) Sequence of events in arm C: rapid HCV antibody followed by same-day treatment with DAAs. (D) Sequence of events in the control arm: standard of care. DAAs, direct-acting antivirals; HCV, hepatitis C virus.

All participants will be administered a clinical and behavioural questionnaire at their baseline visit. All arms are outlined in detail below.

#### Arm A: rapid POC antibody+SOC

##### Baseline visit

Participants will receive an OraQuick rapid HCV antibody test using a fingerstick specimen, according to the manufacturer’s instructions, with the result documented at 20 min. The result will be provided to the participant as a preliminary result with laboratory testing on a venous sample required to confirm the POC test result. If the POC result is positive, blood samples will be collected for any confirmatory laboratory antibody and RNA testing and SOC pretreatment screening. If the POC result is negative, confirmatory testing will be offered but the participant is given the option to decline.

##### Week 0–2 (confirmatory lab results)

If the confirmatory laboratory HCV antibody result is negative, the nurse will communicate this to the participant. The participant will complete the study here. Standard harm minimisation messaging and window periods for detection of HCV will be discussed with the participant.If the confirmatory laboratory HCV antibody result is positive and the RNA result is negative, the nurse will contact the participant by phone to inform them of their result—prior exposure to HCV, no current infection. The participant will complete the study here.If the confirmatory laboratory HCV antibody result is positive and the RNA result is positive, the nurse will contact the participant by phone to inform them of their result of current HCV infection and arrange a follow-up appointment to discuss treatment as per the clinic usual SOC.

##### Weeks 2–12 (HCV RNA positive)

HCV RNA positive participants will be followed up as per usual clinic SOC.

##### Week 12 (HCV RNA positive)

The study nurse will review the medical records of consented participants to determine whether participants with HCV were provided with a DAA prescription within 12 weeks of enrolment in the study.All participants who have been provided with a DAA prescription will be contacted by the study nurse to ask whether they started treatment and if so, when.

##### 12 weeks following treatment completion (sustained virological response or cure assessment):

The medical records of all participants confirmed through medical record review to have started DAA treatment will be reviewed to determine if they have had a sustained virological response (SVR) blood test anytime from 4 to 12 weeks following their treatment completion date.^33^ Reinfection will be differentiated from treatment failure due to relapse by assessing (1) genotype or subtype and (2) viral sequencing at a reference laboratory, whenever possible.Participants who have not had an SVR visit will be contacted by the study nurse approximately 12 weeks following the scheduled treatment completion date (determined by the date they received their script and duration of treatment) to request that they attend an SVR visit.

#### Arm B: rapid POC antibody+rapid POC RNA+SOC

##### Baseline visit

Participants will receive an OraQuick rapid HCV antibody test using a fingerstick specimen, according to the manufacturer’s instructions, with the result documented at 20 min. The result from the 20 min time point will be provided to the participant as a preliminary result, with laboratory testing on a venous sample required to confirm. Blood samples will be collected for any confirmatory laboratory testing and SOC pretreatment screening.Participants with a negative OraQuick result will be provided with this preliminary result and informed that they will be contacted within the next 2 weeks with any laboratory test results.Participants with a positive OraQuick result will be offered POC RNA testing using the Cepheid GeneXpert HCV RNA fingerstick test. The study nurse will conduct POC RNA testing using a fingerstick blood sample according to the manufacturer’s instructions, with results in ~60 min. The study nurse will determine with the participant how they would like to receive these results—via remaining on site or by phone call. If the HCV POC RNA is negative, the study nurse will inform the participant of their result, either in person or by telephone, and they will be contacted within the next 2 weeks with confirmatory laboratory test results.If the HCV POC RNA is positive, the study nurse will inform the participant of their result either in person or by telephone and they will be contacted within the next 2 weeks with confirmatory laboratory test results.

##### Weeks 0–2 (confirmatory lab results)

If the confirmatory laboratory RNA results are negative, the nurse will inform the participant and the participant will complete the study. Standard harm minimisation messaging and window periods for detection of HCV will be discussed with the participant.If the laboratory HCV RNA is positive, the study nurse will contact the participant to provide their results of current HCV infection and discuss follow-up and treatment according to the practice of the clinic.

##### Weeks 2–12 (HCV RNA positive)

Participants with HCV will be followed up as per usual clinic SOC.

##### Week 12 (HCV RNA positive)

The study nurse will review the medical records of consented participants to determine whether participants with HCV were provided with a DAA prescription within 12 weeks of enrolment in the study.All participants who have been provided with a DAA prescription will be contacted by the study nurse to ask whether they started treatment and if so, when.

##### 12 weeks following treatment completion (SVR)

SVR will be assessed as previously described for arm A.

#### Arm C: same-visit rapid POC antibody+treatment commencement

##### Baseline visit

Participants will receive an OraQuick rapid HCV antibody test using a fingerstick specimen, according to the manufacturer’s instructions, with the result documented at 20 min. The result from the 20 min time point will be provided to the participant as a preliminary result, with laboratory testing on a venous sample required to confirm. Blood samples will be collected for any confirmatory laboratory testing and SOC pretreatment screening.Participants with a negative OraQuick result will be advised that the POC test result will be confirmed by standard pathology results and they will be contacted in 1–2 weeks with these results.Participants with a positive OraQuick result will be provided with 2 weeks of sofosbuvir/velpatasvir (Epclusa) and will be instructed to begin treatment. In this sense, arm C uses presumptive treatment, where 14 days of treatment will be dispensed prior to laboratory confirmed diagnosis.^34^ Blood samples will be sent for confirmatory HCV antibody and RNA testing. Participants of childbearing potential will be screened for possible pregnancy and if indicated, a urinary pregnancy test will be performed before dispensing Epclusa. If the pregnancy test is positive, they will not be provided with a study drug and will be referred to SOC. Medical records will be reviewed for potential drug-drug interactions with Epclusa, and participants will be asked about medications they are currently taking. Participants taking medications with red or orange drug–drug interactions will not be provided with a study drug and will be referred to SOC.

##### Weeks 1–2 (confirmatory results)

Participants will be contacted with the results of their confirmatory laboratory blood tests. Participants with a positive confirmatory antibody and negative RNA test result will be contacted with this result of prior exposure, no current infection and instructed to discontinue treatment and dispose of any unused medications. They will complete the study here. Standard harm minimisation messaging and window periods for detection of HCV will be discussed with the participant.Participants with a positive confirmatory antibody and positive confirmatory RNA result will be contacted to arrange ongoing treatment through the study, a further 4 weeks of sofosbuvir/velpatasvir will be dispensed. Further assessment may be required based on the laboratory blood test results:If the participant received an Aspartate Animotransferaese (AST):Platelet Ratio Index score of <1.0, they will be instructed to continue treatment as they were originally instructed.If the participant received an AST:Platelet Ratio Index score of ≥1.0, they will be instructed to continue taking the DAAs and will be referred to a specialised.Participants found to have renal impairment (estimated glomerular filtration rate (eGFR) <30 mL/min) or coinfected with chronic hepatitis B will be instructed to cease treatment and will be referred to a specialist.Participants found to have HIV infection will be instructed to continue the DAAs and be referred to a specialist.

Following specialist assessment, the participant may be required to change medications or alter their treatment course, according to the specialist’s recommendations.

##### Week 6 (HCV RNA positive)

Participants on treatment will be asked to attend a follow-up appointment where they will be provided with a further 4 weeks of sofosbuvir/velpatasvir.

##### Week 10 (HCV RNA positive)

Participants who have received 10 weeks of treatment will be contacted to arrange a follow-up appointment to receive the final 2 weeks of treatment.

##### 12 weeks following treatment completion (SVR)

SVR will be assessed as previously described for arm A.

#### Control arm: SOC testing and treatment

All participants will be tested, treated and followed up according to the usual practice of the clinic for delivery of test results and ongoing HCV treatment. The participants’ medical record will be reviewed at the study close to assess testing and treatment uptake.

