## Methods and analysis

### Trial design

A clustered randomised cross-over trial with six treatment sequences will evaluate the effects of rapid POC testing on retention of participants with HCV care and achievement of cure. Each site will have a standard of care (SOC) control period randomly occurring before or after one of three intervention arms, allowing for intrasite comparison. Each site will have an SOC control period randomly occurring before or after one of the three intervention arms, allowing for intrasite and intersite comparisons to be combined in the estimation of treatment effects. The cross-over design has advantages in ensuring that any external changes that occur over time can be accounted for, which a simple before and after intervention comparison would not allow. External changes might occur at the clinic level, such as services and staff becoming more aware or skilled in offering HCV testing, or they may occur at a system level, such as changes in access to testing, care or treatment. There will be a 1-month washout period between arms at each study site. Participant recruitment began in March 2022 and is intended to continue for up to 24 months.

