### Study outcomes

The two primary outcomes of this trial include:

The proportion of participants commencing HCV treatment in each arm. Commencement of HCV treatment is defined as receipt of a script for treatment in arms A, B and control and as commencement of treatment with study drug in arm C. The proportion commencing treatment in each intervention arm will be compared with the control arm.The proportion of participants with HCV who start treatment achieving cure. Cure will be assessed by review of medical records for a clinic visit to assess SVR; if no visit has taken place, the study nurse will contact the participant to arrange one in all arms except the control.

Commencing treatment is an important and easily measurable outcome in clinical practice. The rationale for two primary outcomes is that arm C itself involves providing treatment to everyone found to have HCV as part of its intervention.

Secondary outcomes of this study include:

Time to treatment commencement is defined as number of days from first test to first dose of treatment.Case finding is defined as the proportion of people diagnosed with HCV among all those recruited.Cost-effectiveness is defined as the incremental cost to find and commence treatment among one person living with HCV from a health system perspective.

Participant acceptability is based on qualitative evaluation subject to further substudy design and ethical approval.

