### Sample size

Comparisons of primary interest are comparing outcome 1 (treatment commencement) in control and arm A; outcome 1 in control and arm B; and outcome 2 (HCV cure) in control and arm C. We consider sample size calculations with a minimum of 80% power and a significance level of 0.05/3=0.0167. Comparisons of control versus A are expected to result in the smallest required sample sizes so sample size calculations focus on this comparison. We use the Shiny CRT app^36^ for sample size calculations, assuming that the t- distribution is used instead of the normal approximation (accounting for small numbers of clusters).^37^

We suppose that five sites are assigned to each of the six treatment sequences. We found that with 24 participants recruited in each cluster in each period, power will be greater than 80% to detect a change in proportions of participants starting HCV treatment of 30%–50% where 10 clusters are allocated to arm A. Due to the greater portion of participants expected to start treatment in arm B (70%) and arm C (90%), power >80% is achieved with eight clusters assigned to the sequences that involve arms B or C (ie, with four clusters randomised to each of the arm B then control; control then arm B; Arm C then control; and control then arm C sequences). The proportion of participants expected to achieve cure in each arm are 10% among controls, 30% in arm A, 50% in arm B and 70% in arm C. Allowing for 20% loss to follow-up of sites and of participants, 30 participants per site per period would need to be recruited. Given these results, we will instruct sites to aim for 40 participants per site per period to counteract instances where some sites are unable to achieve 30 participants per site per period; some sites achieving 40 participants will balance sites which achieve <30. This would imply a maximum total of 2400 participants would need to be recruited.

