### Statistical analysis

Results from the trial will be reported according to the CONSORT extension statement for cluster randomised trials,^38^ or a CONSORT extension statement for cluster randomised crossover trials if one is available prior to end of data collection. Clinic and patient demographics will be described by site and study period. Analyses will be conducted on an intention-to-treat basis, with patients analysed according to the randomised treatment of their cluster at the time of their inclusion in the study. All available binary outcomes will be analysed at the patient level using mixed-effects logistic regression models with random intercepts for clinic and clinic period and fixed effects for interventions.^39^ ORs and 95% CIs will be reported; in addition, we will calculate and report risk differences and 95% CIs.

There are three main comparisons proposed, namely, treatment uptake outcome in arm A versus control (comparison 1) and arm B versus control (comparison 2) and HCV cure in Arm C versus control (comparison 3). Incremental benefits of arm B to arm A, and arm C to arm B, and arm C to arm A on treatment uptake and HCV cure will be performed in subgroup analyses. Data from controls in each arm will be pooled and a single model fitted for each outcome.

Randomisation will occur in batches of six, performed by the coordinating centre and concealed from investigators and sites until after site governance approcal. Since randomisation is occurring within batches of six services, fixed effects for batch will be included in these models. The Kenward-Roger correction will be applied to adjust for the small number of clinics.^40^ Estimates of intracluster correlations (within-period and between-period) will be reported. Time-to-event outcomes such as time to complete diagnosis will be analysed using Cox proportional hazards models with shared-frailty terms for site and fixed terms for treatment group and randomisation batch. There may be imbalances between sites with respect to various clinic and patient-level characteristics, and secondary analyses will adjust for these.

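### Outcome 1 is checked within 12 weeks of enrolment in arms A and B but at study close, with no stated limit, in control; no common window is set, which may bias comparisons 1 and 2 against the intervention

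*Protocol article*

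**What the plan says.** For arms A and B, the sections headed Week 12 (HCV RNA positive) have the study nurse check the records to see whether participants with HCV "were provided with a DAA prescription within 12 weeks of enrolment in the study". This is the only review of scripts described for those arms.

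For control, the section Control arm: SOC testing and treatment says the "medical record will be reviewed at the study close to assess testing and treatment uptake". It gives no interval from enrolment.

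Study outcomes defines the event but not the period: "Commencement of HCV treatment is defined as receipt of a script for treatment in arms A, B and control". In arm C the event is the start of study drug.

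Sample size names the comparisons of primary interest on this outcome: "outcome 1 (treatment commencement) in control and arm A; outcome 1 in control and arm B". Statistical analysis adds: "Data from controls in each arm will be pooled and a single model fitted for each outcome". Outcome 1 is binary and analysed by mixed-effects logistic regression, with patients analysed by their cluster's allocation at inclusion.

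On timing, Trial design says: "There will be a 1-month washout period between arms at each study site". It also says that recruitment is "intended to continue for up to 24 months", whereas the abstract gives 9 March 2022 to an expected December 2024.

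**The concern.** The two sides of comparisons 1 and 2 are ascertained at different times. If control scripts are counted up to the review date, a control participant who gets a script in month 6 is a success, while an arm A participant who does the same is a failure. Control uptake is then overstated relative to A and B, and the estimated effects move toward zero.

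Two features make this harder to repair afterwards. First, time from enrolment to study close depends on when a participant enrolled, so the extra control time is not constant. Second, at sites randomised to control first, the clinic moves to a point-of-care arm after the washout. A script issued then to a former control participant still counts for control, because analysis follows the allocation at inclusion.

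The listed model does not correct this. Its terms are intervention, batch, clinic and clinic-period, with none for length of follow-up. A random clinic-period intercept does not absorb a systematic difference between control and intervention periods. The best-worst and worst-best analyses address missing outcomes, not unequal windows.

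**Working it through.** **The text, side by side (outcome 1)**

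| Arm | Event | When read | Limit on script date |
|---|---|---|---|
| A | script | week 12 | 12 weeks from enrolment |
| B | script | week 12 | 12 weeks from enrolment |
| Control | script | study close | none stated |
| Study outcomes section | script (study-drug start in C) | not stated | none stated |

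**Planning inputs (Sample size).** Uptake is 30% in control, 50% in A and 70% in B. There are 24 participants per cluster-period, 10 clusters for A and 8 for B, and alpha is 0.05/3 = 0.0167. The planned differences are 50 − 30 = 20 points for A and 70 − 30 = 40 points for B.

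**The plan's own power figure.** The stated power for A is above 80%. The article gives no intracluster correlation (ICC) or cluster autocorrelation (CAC), so the figure can be shown to be attainable but not confirmed. I used

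Var = [2·p(1−p)/(m·K)] · [1 + (m−1)·ICC − m·ICC·CAC],

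with p(1−p) averaged over the two arms, two-sided alpha 0.0167, and power approximated as P(T ≤ d − c), where d is the difference divided by its standard error and T and the critical value c have K − 2 degrees of freedom. For A at ICC 0.05 and CAC 0.8:

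- p(1−p) = (0.21 + 0.25)/2 = 0.23
- bracket = 1 + 1.15 − 0.96 = 1.19
- Var = 2 × 0.23/240 × 1.19 = 0.00228
- power 86%

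At ICC 0.10 and CAC 0.8 power is 80%; at ICC 0.10 and CAC 0.5 it is 55%. The rest uses the first two settings, which agree with the plan's claim to rounding.

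**Effect of late control scripts.** Assume that the planned 30% is uptake by 12 weeks; the article attaches no time point to it. If a fraction q of the 70% untreated at week 12 later gets a script, control reads 0.30 + 0.70q:

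- q = 10%: 0.30 + 0.07 = 37%
- q = 20%: 0.30 + 0.14 = 44%
- q = 28.6%: 0.30 + 0.20 = 50%, and the A difference is zero
- q = 57%: 0.30 + 0.40 = 70%, and the B difference is zero

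**Consequence for power (ICC 0.05–0.10, CAC 0.8)**

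| Control reads | A: difference, OR | A: power | B: difference | B: power |
|---|---|---|---|---|
| 30% | 20 points, 2.33 | 80–86% | 40 points | >99% |
| 35% | 15 points, 1.86 | 44–53% | 35 points | about 99% |
| 40% | 10 points, 1.50 | 15–18% | 30 points | 95–97% |
| 50% | 0, 1.00 | none | 20 points | 57–67% |

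**How uptake might continue (illustration only).** With F(t) = 1 − 0.70^((t/12)^k), control uptake at 24 and 52 weeks is 51% and 79% for k = 1 (constant hazard), 40% and 52% for k = 0.5, and 36% and 43% for k = 0.3. The shapes are assumptions. The spread shows how little can be said about the real size.

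**Overlap with period 2.** Taking the washout as 4 weeks, even a 12-week window runs up to 12 − 4 = 8 weeks into period 2 for the last period-1 enrolees. An open window can do so for any control-first participant.

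**The case against.** The strongest reply is that study close is when control records are read, not a rule about which scripts count. A late review can apply a 12-week cut-off to dated scripts, and the full protocol or analysis plan may say so. This stands in part: a reader might infer that the plan fixes a longer control window, and it does not say that. It neither counts nor excludes control scripts after week 12, and study close could mean close of the trial, the site or the participant's follow-up. But the article does more than omit a detail. It gives a window for two arms, a different review time for their comparator, and an outcome definition that does not reconcile them.

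A reader might also infer that comparisons 1 and 2 would be reversed. The document does not support that. Reversal needs control above 50% for A and above 70% for B, against a planned 30%, and late uptake is not reported. The Introduction cites 32% of antibody-positive survey participants as having accessed treatment up to 2020. That population and denominator differ, but the figure suggests slowing uptake and makes the constant-hazard projection look high. For B, only that projection at one year (79%) passes 70%.

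Nor is contamination by the intervention in period 2 shown. The point-of-care tests are delivered at an enrolled participant's baseline visit, and testing in the past 3 months is an exclusion, which limits early re-entry. Later re-entry and clinic-level spill-over are neither stated nor excluded.

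**Conclusion.** The mismatch is in the text and affects the primary outcome of two of the three main comparisons. Followed literally, it gives control a longer and variable window, which may bias the A and B effects toward no benefit. Comparison 1 is sensitive: under the assumed ICC and CAC, a 5-point rise in control takes its power from 80–86% to 44–53%, and a 20-point rise removes the planned difference. Comparison 2 tolerates moderate drift, keeping 95–97% power with control at 40%.

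These figures assume that the planned 30% is a 12-week proportion and that A and B hold at 50% and 70%. The true size depends on how many control scripts are issued after week 12 and on how the reviewer treats them, and the article gives neither. The inconsistency is certain; the amount of bias is not known. It should be settled before outcome data are analysed.

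**What to change.** Reconcile the Week 12 sections for arms A and B, the control arm section and Study outcomes. Define outcome 1 in every arm with one common window from enrolment, for example the 12 weeks already used for A and B. Apply it to the date of the script (the date study drug was started in arm C), whenever the record review takes place. Control records can still be read at study close, with only scripts dated inside the window counting. Report later scripts as a secondary outcome.

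A sensitivity analysis that leaves out period-1 participants whose window crosses into period 2 is optional. It addresses carry-over that would remain even with a common window.

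The cost is about one sentence in the outcome definition and a date field in the control record review. No extra participants or visits are needed. The change concerns outcome measurement only, not clinical management.
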